## Supplement 1. Trial protocol and statistical analysis plan

### Trial registered on ANZCTR

|                                                |                                                                                   |                          |
|------------------------------------------------|-----------------------------------------------------------------------------------|--------------------------|
| Registration number                            | [figure not shown] | ACTRN12621000253808      |
| Ethics application status                      | [figure not shown] | Approved                 |
| Date submitted                                 | [figure not shown] | 1/01/2021                |
| Date registered                                | [figure not shown] | 9/03/2021                |
| Date last updated                              | [figure not shown] | 10/11/2021               |
| Date data sharing statement initially provided | [figure not shown] | 9/03/2021                |
| Date results information initially provided    | [figure not shown] | 10/11/2021               |
| Type of registration                           | [figure not shown] | Prospectively registered |

#### Titles & IDs

---

|                              |                                                                                                                                                                                    |
|------------------------------|------------------------------------------------------------------------------------------------------------------------------------------------------------------------------------|
| Public title                 | Examination of Australian women's intentions and psychological outcomes related to breast density notification with mammography screening results: An online randomised experiment |
| Scientific title             | Examination of Australian women's intentions and psychological outcomes related to breast density notification with mammography screening results: An online randomised experiment |
| Secondary ID [1]             | Nil known                                                                                                                                                                          |
| Universal Trial Number (UTN) |                                                                                                                                                                                    |
| Trial acronym                |                                                                                                                                                                                    |
| Linked study record          |                                                                                                                                                                                    |

#### Health condition

---

##### Health condition(s) or problem(s) studied:

Breast density

Breast cancer screening

Breast cancer

##### Condition category

Public Health

Cancer

##### Condition code

Other public health

Breast

**Study type**

Interventional

**Description of intervention(s) /exposure**

This study aims to quantitatively assess how different formats of information provision on breast density affect women's screening intentions, psychological outcomes (anxiety and breast cancer worry) and knowledge of breast density.

This study will use a 3-arm randomised trial design. This trial will be conducted online through a survey platform. An online sample of Australian women (outside of Western Australia) will be recruited through a large market research organisation. Women will be aged between 40 to 74 years with no prior history of breast cancer or ductal carcinoma in situ (DCIS). Women will not be required to have undergone screening mammogram prior to participating in this study.

Women will be presented with a hypothetical scenario in which they were asked to imagine going for a routine mammogram screening and receiving a letter about their mammogram results. Women then will be randomised to be shown one of three example letters (written format) about mammography results.

Arm 1: Control group (standard screening mammogram result)

Women in the control group will be shown a standard screening mammogram result letter, which will show a "clear" result, i.e., no breast cancer could be seen on the mammogram. This letter will be similar to the ones that breast screening services in Australia send out to women with 'clear' results.

Arm 2: Intervention 1 (standard screening mammogram result + existing breast density notification messaging (e.g. WA))

Women in the intervention 1 will be shown the same letter as the control group, along with an additional breast density notification letter for women with dense breasts. This breast density letter will be identical to the ones that screening services in Western Australia send out to women who are found to have dense breast tissue. This letter includes information that the woman's breast tissue is dense, followed by information on what breast density means, its implications and following up with a GP.

Arm 3: Intervention 2 (standard screening mammogram + health literacy sensitive breast density messaging)

Women in the intervention 2 will be shown the same letter as the control group, along with an additional breast density notification letter for women with dense breasts. This letter will be developed by the research team and will be health literacy appropriate, i.e. tailored for a reading level of grade 8. It will also incorporate health literacy strategies such as avoiding complex medical terminologies, using spaces and images or icons. This letter will include information such as woman's breast density level, what is breast density and its implications, what can be done, what are the pros and cons of additional testing and speaking with a healthcare provider.

The online intervention will be administered once only with no repeat or subsequent sessions upon completion. It will take 10-15 minutes for participants to take part in the study.

Adherence to the intervention will be ensured by forcing a response for outcome measurement items that follow the intervention and by monitoring the overall time taken to complete the online study.

**Intervention code [1]**

Behaviour

**Comparator / control treatment**

The control group will be randomised to receive a screening mammogram result without the breast density messaging.

**Control group**

Active

**Outcomes**

---

**Primary outcome [1]**

## Screening intention

This outcome is a composite outcome comprising of four elements: intention to go for extra tests, choice of extra tests, intention to change screening frequency and intended change in screening frequency (increase or decrease).

Participants will be asked if they would go for extra tests (supplemental screening) after receiving the intervention or control messaging (Yes/No/Don't know). If they choose yes, they will be further prompted to choose which extra test (ultrasound, MRI, ultrasound and MRI, tomosynthesis, or other) they would go for. Participants will be asked whether they would change how often they go for screening mammogram after receiving the intervention or control messaging (Yes/No/Don't know) and if yes, whether they would go more frequently or less frequently.

***Timepoint [1]***

Immediately after intervention

**Primary outcome [2]**

## Anxiety

The following item will be used to measure anxiety.

Please indicate the extent of your agreement or disagreement with the following statements. Receiving this letter does/would make me feel anxious (uneasy, worried, nervous)\*

4-point scale (1 = 'strongly agree' to 4 = 'strongly disagree')

Reference: Rhodes DJ, Jenkins SM, Hruska CB, et al. Breast Density Awareness, Knowledge, and Attitudes Among US Women: National Survey Results Across 5 Years. J Am Coll Radiol 2020;17(3):391-404. doi: 10.1016/j.jacr.2019.11.003 [published Online First: 2019/11/23]

**Timepoint [2]**

Immediately after intervention

**Primary outcome [3]**

Breast cancer worry

The following item will be used to measure breast cancer worry.

How worried would you be about developing breast cancer after receiving this letter? 4-point scale (1 = 'strongly agree' to 4 = 'strongly disagree')

Reference: Sutton S, Bickler G, Sancho-Aldridge J, Saidi G. Prospective study of predictors of attendance for breast screening in inner London. Journal of Epidemiology & Community Health. 1994;48(1):65-73.

**Timepoint [3]**

Immediately after intervention

**Secondary outcome [1]**

Breast density-related knowledge

This outcome is a composite outcome comprising of four elements: knowledge of the prevalence of women with dense breasts, knowledge that breast density is an independent risk factor of breast cancer, knowledge of dense breast tissue's masking effect on a mammogram and knowledge of breast density change with age.

Breast density-related knowledge will be measured using both the custom-designed and previously validated items. The items will measure participants' knowledge in relation to the prevalence of women with dense breasts, breast density being an independent risk factor of breast cancer, breast density masking effect on a mammogram and change with age.

Reference: Rhodes DJ, Jenkins SM, Hruska CB, et al. Breast Density Awareness, Knowledge, and Attitudes Among US Women: National Survey Results Across 5 Years. J Am Coll Radiol 2020;17(3):391-404.

**Timepoint [1]**

Immediately after intervention

**Secondary outcome [2]**

Intention to talk to a doctor about breast density will be measured using a single item.

Would you plan to talk to your doctor or nurse about this letter? Yes/No/Don't know

**Timepoint [2]**

Immediately after intervention

**Secondary outcome [3]**

Breast cancer perceived risk will be measured using the following items:

What do you think is your chance of getting breast cancer in your lifetime if you received this letter? Below average/Average/Above average

Compared to other people your age, race and sex, what do you think is your chance of getting breast cancer in your lifetime if you received this letter? Below average/Average/Above average

Reference: Lipkus IM, Kuchibhatla M, McBride CM, Bosworth HB, Pollak KI, Siegler IC, et al. Relationships among Breast Cancer Perceived Absolute Risk, Comparative Risk, and Worries. Cancer Epidemiology Biomarkers & Prevention. 2000;9(9):973-975.

**Timepoint [3]**

Immediately after the intervention

**Secondary outcome [4]**

Other psychological impacts of breast density messaging will be measured using the following items: The following item will be used to measure anxiety.

Please indicate the extent of your agreement or disagreement with the following statements. Receiving this letter does/would make me feel informed to make decisions regarding my breast health 4-point scale (1 = 'strongly agree' to 4 = 'strongly disagree')

Receiving this letter does/would make me feel confused about what to do regarding my breast health4-point scale (1 = ‘strongly agree’ to 4 = ‘strongly disagree’)

Reference: Rhodes DJ, Jenkins SM, Hruska CB, et al. Breast Density Awareness, Knowledge, and Attitudes Among US Women: National Survey Results Across 5 Years. J Am Coll Radiol 2020;17(3):391-404. doi: 10.1016/j.jacr.2019.11.003 [published Online First: 2019/11/23]

***Timepoint [4]***

Immediately after the intervention

**Eligibility**

---

**Key inclusion criteria**

Australian women aged 40-74, live outside Western Australia and no prior history of breast cancer or DCIS. Women will not be required to have undergone a screening mammogram prior to participation in the study.

**Minimum age**

40 Years

|                                            |                                                                                                     |
|--------------------------------------------|-----------------------------------------------------------------------------------------------------|
| Maximum age                         | 74 Years                                                                                            |
| Gender                              | Females                                                                                             |
| Can healthy volunteers participate? | Yes                                                                                                 |
| Key exclusion criteria
DCIS      | Male, aged under 40 or over 74, lives in Western Australia, has a prior history of breast cancer or |

## Study design

|                                                                                                           |                                                                                                                                                                                                                                                                                                                                                                                                                                |
|-----------------------------------------------------------------------------------------------------------|--------------------------------------------------------------------------------------------------------------------------------------------------------------------------------------------------------------------------------------------------------------------------------------------------------------------------------------------------------------------------------------------------------------------------------|
| Purpose of the study                                                                               | Educational / counselling / training                                                                                                                                                                                                                                                                                                                                                                                           |
| Allocation to intervention                                                                         | Randomised controlled trial                                                                                                                                                                                                                                                                                                                                                                                                    |
| Procedure for enrolling a subject and allocating the treatment (allocation concealment procedures) | Central randomisation by computer using Qualtrics survey software.

Researchers will have no direct contact with participants. Once a participant agrees to take part in the study they will be randomly assigned to be immediately sent a questionnaire containing either one of two versions of the intervention or the control.                                                                                       |
| Methods used to generate the sequence in which subjects will be randomised (sequence generation)   | Qualtrics computer software will randomly allocate each participant to one of the arms of the trial as they enter the study.                                                                                                                                                                                                                                                                                                   |
| Masking / blinding                                                                                 | Blinded (masking used)                                                                                                                                                                                                                                                                                                                                                                                                         |
| Who is / are masked / blinded?                                                                     | The people receiving the treatment/s
The people administering the treatment/s                                                                                                                                                                                                                                                                                                                                               |
| Intervention assignment                                                                            | Parallel                                                                                                                                                                                                                                                                                                                                                                                                                       |
| Other design features                                                                              |                                                                                                                                                                                                                                                                                                                                                                                                                                |
| Phase                                                                                              | Not Applicable                                                                                                                                                                                                                                                                                                                                                                                                                 |
| Type of endpoint(s)                                                                                | Efficacy                                                                                                                                                                                                                                                                                                                                                                                                                       |
| Statistical methods / analysis                                                                     | The proposed sample (n=1398) provides 80% with an adjusted alpha of 0.025 to account for multiple comparisons between either intervention arm and the control. Statistical analysis will be conducted using planned contrasts between intervention arms and control and implemented in regression models. All data will be analysed by researchers at the University of Sydney and compiled for publication and dissemination. |

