### Specific research questions:

1. Do outcomes relating to intention to seek supplemental screening, feelings of being anxious, informed or confused, breast cancer worry, breast density knowledge, cancer risk perception and intention to speak to a GP differ between women who received screening mammography results with or without breast density messaging?
2. Do outcomes relating to intention to seek supplemental screening, feelings of being anxious, informed or confused, breast cancer worry, breast density knowledge, cancer risk perception and intention to speak to a GP differ between women who received existing breast density notification messaging and health literacy sensitive breast density messaging?
3. Do women's breast cancer worry differ before and after the breast density notification?  
Does the difference vary depending on which messaging they receive?
  - Intervention (*condition=2* or *condition=3*)
  - Cancer worry before intervention (*CancWorryBefore*)
  - Cancer worry after intervention (*CancWorryAfter*)

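### The 0.025 split leaves the letter-versus-letter contrast with no error rule; a gated test built on the same split would cover all three contrasts per outcome, at a stated cost to question 2

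*Combined protocol and SAP*

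**What the plan says.** The registry entry describes three arms: a control letter (arm 1), the existing density notification (arm 2) and a health literacy sensitive notification (arm 3). Under Study design, the statistical methods row justifies the sample size with "an adjusted alpha of 0.025 to account for multiple comparisons between either intervention arm and the control". It then describes the analysis as "planned contrasts between intervention arms and control and implemented in regression models". Only the two contrasts with control are named there.

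The SAP poses two between-arm questions. Question 1 asks whether outcomes "differ between women who received screening mammography results with or without breast density messaging". Question 2 asks whether they "differ between women who received existing breast density notification messaging and health literacy sensitive breast density messaging". Question 2 lists the same outcomes as question 1, primary and secondary. The SAP assigns no alpha, gate or multiplicity rule to it, and neither part of the document describes a stepwise or closed procedure.

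**The concern.** The sponsor chose to protect against multiple pairwise comparisons, then asked a third pairwise question outside that protection. The third question is the head-to-head of the two letters, a main reason for having a third arm. Without a rule, a positive answer to it has no stated error rate alongside the other two contrasts.

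The single-step split also gives up some power. With only three arms, 0.025 need not be kept for every contrast once one of them has shown that the arms are not all equal.

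**Working it through.** **Inputs.** Alpha of 0.025 per control contrast, 80% power and N = 1398 come from the registry entry: "The proposed sample (n=1398) provides 80% with an adjusted alpha of 0.025". The following are not stated and are assumed: overall alpha 0.05, two-sided tests (the questions ask whether outcomes differ), and 1:1:1 allocation, so 1398/3 = 466 per arm. I take question 1 as two separate contrasts, following the registry entry.

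**The plan's own figures.** 0.05/2 = 0.025, so the alpha is a Bonferroni split over two contrasts. N cannot be rebuilt from stated inputs because no effect size is given. Under an assumed 50% v 60%, the unpooled formula gives (2.241 + 0.842)² × (0.25 + 0.24)/0.10² = 465.7, so 466 per arm and 1398 in all. The pooled formula gives 470 × 3 = 1410, and an assumed standardised difference of 0.20 gives 476 × 3 = 1428. The power results below need no effect size, only the noncentrality that gives 80% power at two-sided 0.025: 2.241 + 0.842 = 3.083. I call this the reference effect.

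**Error per outcome when all arms are equal** (simulated; the two control contrasts correlate 0.5):
- two control contrasts at 0.025: 4.6%
- adding arm 2 v arm 3 at 0.025: 6.4%
- adding arm 2 v arm 3 at 0.05: 8.5%

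**Gated rule.** Step 1: proceed only if at least one letter-versus-control p ≤ 0.025. Step 2: test all three contrasts at 0.05.
- *Error.* If any two arm equalities hold, so does the third. So either all arms are equal, and step 1 passes with probability at most 5% (4.6% simulated), or at most one pairwise null is true, and it is tested at 0.05. The largest simulated error was 5.0%.
- *No control result lost.* A control p ≤ 0.025 passes step 1 by itself and is also below 0.05. None was lost in 4 million draws in any scenario.

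**Power against control**

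| Scenario | Result | Single-step 0.025 | Gated rule |
|---|---|---|---|
| Both letters at reference effect | Each contrast | 80.0% | 84.5% |
| | Both contrasts | 68.7% | 77.8% |
| | At least one | 91.3% | 91.3% |
| Arm 3 at half of arm 2's effect | Arm 3 v control | 24% | 33% |

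**Power for arm 2 v arm 3**

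| Scenario | Ungated 0.025 | Ungated 0.05 | Gated rule | Plain 0.05/3 |
|---|---|---|---|---|
| Arm 3 at double arm 2's effect | 80% | 87% | 87% | 75% |
| Only arm 2 acts | 80% | 87% | 74% | 75% |
| Half the effect each, opposite directions | 80% | 87% | 46% | 75% |

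The ungated figures are Φ(3.083 − 2.241) = 0.800 and Φ(3.083 − 1.960) = 0.869. A plain 0.05/3 split would also cut each control contrast from 80% to 75%.

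**False positives for a null letter.** When one letter has the reference effect and the other none, false rejection of the null letter against control rises from 2.5% to 4.2%. It approaches 5% as the working letter's effect grows.

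**The case against.** Several points on the other side stand.

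- *The 0.025 rule is partly inferred.* It is attached to the sample-size statement; the analysis sentence and the SAP give no alpha. A reader might infer that the plan as written exceeds 5%. The documents do not support that: 6.4% and 8.5% each depend on an alpha for question 2 that is never stated. The gap in the text is the missing rule.
- *The split is valid.* Bonferroni over two contrasts delivers the 80% claimed, and the chance of at least one control finding does not change. The registry entry reports 1505 recruited. If all are analysed in equal arms, single-step power at the reference effect is Φ(3.083 × √(1505/1398) − 2.241) = Φ(0.958), about 83%, so the need is smaller.
- *The gate ranks question 1 above question 2*, which the SAP does not do. The cost is largest when the letters lie on opposite sides of control. That is plausible for feeling informed and feeling confused, both SAP primary outcomes, since arm 3 is written to be easier to understand.
- *Other outcomes.* The registry lists three primary outcomes and the SAP five primary variables, with no rule across them. Five independent null contrasts give 1 − 0.975⁵ = 12% at 0.025, and as much as 1 − 0.95⁵ = 23% at 0.05. The gated rule does not address this, and it loosens the threshold for a null letter when the other letter works.
- *Timing.* Data collection ended on 30/08/2021 and the SAP shown is undated. Loosening 0.025 to 0.05 after results were seen would be post hoc.

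None of this undoes the logic of the rule. It limits the claim and sets conditions on its use.

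**Conclusion.** The point holds as a worthwhile improvement, not as a fatal flaw. Question 2 lies outside the stated error control, and a rule built on the same 0.025 would bring it inside at 5% or less per outcome. For the control contrasts the gain is moderate: about 4.5 points of power each and 9 points for both, with no result forfeited. A reader might conclude that the gated rule is better in every respect. It is not: it loses nothing for the contrasts with control, but question 2 can lose a good deal.

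The figures rest on two-sided testing, overall alpha 0.05, equal allocation, and all three contrasts being taken from the same model parameter, without which two equalities do not imply the third. Multiplicity across primary outcomes stays open.

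**What to change.** Add to the SAP, for each primary outcome:

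1. If either letter-versus-control p ≤ 0.025, test arm 2 v control, arm 3 v control and arm 2 v arm 3 each at 0.05; otherwise declare none.
2. Take all three contrasts from one model and the same parameter.
3. State how confidence intervals will be formed, since they do not follow directly from this rule.
4. State that question 2 is gated, with the power cost above, and that the rule does not cover multiplicity across outcomes.

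If the sponsor does not want to gate question 2, use the step-down for the two control contrasts only (smaller p at 0.025, then the other at 0.05), and label arm 2 v arm 3 as outside error control. The gain against control is the same.

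Either rule is confirmatory only if fixed before arm-level results are seen. Otherwise, keep 0.025 for the control contrasts, label question 2 as uncontrolled, and report the gated result as a sensitivity analysis.

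The cost is a short SAP paragraph and an interval rule. It needs no further participants, and the sample-size basis can stay as stated.

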### Outcome measures:

Variable name in SPSS in *light blue*

Variable for comparison: condition (*condition*)

Primary outcomes:

- intentions to seek supplemental screening (*Intent\_Screen\_SuppScreen*)
- psychological outcomes
  - feeling anxious (*Anxiety*)
  - feeling informed (*Informed*)
  - feeling confused (*Confusion*)
- breast cancer worry (*CancWorryAfter*)

Secondary outcomes:

- intention to speak to a GP (*Intent\_TalkGP*)
- breast density knowledge
  - Knowledge about percentage (*BDKnowl\_Percentage*)
  - Knowledge about cancer risk (*BDKnowl\_CancRisk*)
  - Knowledge about masking (*BDKnowl\_Masking*)
  - Knowledge about age (*BDKnowl\_Age*)
- Cancer risk perception (*Percep\_CancRisk*)

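### The 0.025 alpha allows for two comparisons with control on one outcome; no rule covers the three (registry) or five (SAP) primary outcomes or the comparison of the two letters

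*Combined protocol and SAP*

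**What the plan says.** The registry record (*Study design*, statistical methods entry) gives the only error-rate statement in the documents: "The proposed sample (n=1398) provides 80% with an adjusted alpha of 0.025". The adjustment is described as an "adjusted alpha of 0.025 to account for multiple comparisons between either intervention arm and the control". The same entry describes the analysis as "planned contrasts between intervention arms and control and implemented in regression models". It gives no effect size, control rate, allocation ratio or sidedness, and does not say which outcome the sample size serves.

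The registry lists three primary outcomes: screening intention (a composite of four elements with no scoring rule), anxiety and breast cancer worry.

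The SAP (*Outcome measures*) lists five primary variables: supplemental screening intention, feeling anxious, informed and confused, and breast cancer worry. The registry places informed and confused under secondary outcome [4].

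SAP question 1 asks whether outcomes "differ between women who received screening mammography results with or without breast density messaging". Question 2 asks whether the same outcomes "differ between women who received existing breast density notification messaging and health literacy sensitive breast density messaging". The SAP states no alpha, testing order or multiplicity rule for either question.

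**The concern.** The plan corrects for multiplicity, so it treats at least some of its tests as confirmatory, but the correction covers only part of what is tested. Two contrasts at 0.025 spend a 5% budget on one outcome. The second and later primary outcomes, and the contrast between the two letters, have no share of it. The documents also disagree on whether there are three or five primaries, so the family of tests is not fixed.

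Without a rule, a significant result on any one of 6, 9 or 15 primary tests could be presented as a confirmed effect of notification under an alpha described as adjusted. The actual chance of such a finding under no effect would be well above 5%.

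**Working it through.** **Inputs from the documents.** Three arms; target 1398; 80%; alpha 0.025; final enrolment 1505 (*Recruitment*); three registered or five SAP primaries; two contrasts with control in the registry entry; one further contrast in SAP question 2.

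**Assumptions, not in the documents.** Equal allocation (1398/3 = 466 per arm), two-sided tests, no dropout and, for power only, 50% vs 60% on a binary outcome.

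**Step 1: the stated alpha.** 0.05/2 = 0.025. With two contrasts sharing a control arm, on one outcome, the simulated family-wise error is about 4.6% (bound 2 × 0.025 = 5%). The adjustment works for what it covers.

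**Step 2: the stated sample size.** The documents give no effect size, so 1398 can only be back-solved. Using the unpooled two-proportion formula:

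n per arm = (z₀.₉₈₇₅ + z₀.₈₀)² × [p₁(1−p₁) + p₂(1−p₂)] / (p₁−p₂)² = (2.2414 + 0.8416)² × (0.25 + 0.24) / 0.10² = 9.505 × 49 = 465.7

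This rounds up to 466 per arm, or 1398 in total. The match is not unique: 40% vs 50% gives the same n, and 466 per arm also gives 80% power for a standardised mean difference of about 0.20.

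**Step 3: family-wise error with every test at 0.025.** Trials were simulated with no true effects, three equal arms and exchangeable correlation between outcomes. The contrasts share arms, so their dependence is included. The last column is the bound, number of tests × 0.025.

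| Tests | Correlation 0.7 | Correlation 0 | Bound |
|---|---|---|---|
| 1 outcome × 3 contrasts | 6.4% | 6.4% | 7.5% |
| 3 outcomes × 2 contrasts with control | 10% | 13% | 15% |
| 3 outcomes × 3 contrasts | 14% | 18% | 22.5% |
| 5 outcomes × 3 contrasts | 19% | 28% | 37.5% |

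Question 1 could instead mean one pooled contrast (either letter vs none). That contrast plus question 2 gives 11–14% for three outcomes and 15–22% for five. None of these figures depends on the assumed effect size.

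**Step 4: power per comparison.** Power = Φ(0.10/SE − z₁₋α/₂), with SE = √(0.49/n per arm). For n = 466, SE = 0.03243 and 0.10/SE = 3.084. For 1505/3 = 501.7, SE = 0.03125 and 0.10/SE = 3.200.

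| Alpha per test | z | Power, 466 per arm | Power, 1505 in total |
|---|---|---|---|
| 0.025 | 2.241 | 80.0% | 83.1% |
| 0.05/3 | 2.394 | 75.5% | 79.0% |
| 0.05/9 | 2.773 | 62.2% | 66.5% |
| 0.05/15 | 2.935 | 55.9% | 60.4% |

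The 0.05/9 and 0.05/15 rows are plain Bonferroni. They ignore correlation between outcomes and so show a harsh case.

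**The case against.** The strongest reply is that the plan breaks no promise. It says which comparisons the adjustment covers, never claims 5% error across outcomes, and never says that one significant primary makes the trial a success. Whether distinct primary outcomes need joint control when no joint claim is made is a matter of judgement. This stands: the fault is a multiplicity strategy that stops short and is otherwise unstated.

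The larger error figures also rest on a reading. The registry entry limits planned contrasts to intervention arms against control, and the SAP gives question 2 no alpha. The 14–18% and 19–28% ranges apply only if question 2 is treated as confirmatory. The figure closest to the registry text is 10–13%, which is still at least twice 5%.

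A reader might infer that the 5% error rate and the 80% power both fail. The documents do not support that, because the two are alternatives. With every test at 0.025, power per comparison is unchanged and only family-wise error rises; if alpha is tightened, error is controlled and power falls. Nor do the documents show that the 80% was computed for a binary screening item at 50% vs 60%. That is an inference from an arithmetical match which other inputs also produce.

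**Conclusion.** The point holds as a gap in the multiplicity plan. On every reading examined with three or more primary outcomes, testing each at 0.025 leaves the chance of at least one false positive at about 10% or more. It is 10–13% on the registry's own outcomes and contrasts, and up to 28% with five SAP primaries, three confirmatory contrasts and uncorrelated outcomes. These figures assume equal arms, no true effects and exchangeable correlation between 0 and 0.7.

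The power consequence is conditional. If 50% vs 60% is the design effect, the 80% stands at 0.025. A confirmatory third contrast at 0.05/3 would bring it to about 75% at the target size, or about 79% with the 1505 enrolled.

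**What to change.** Add a multiplicity paragraph to the SAP.

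- Keep 0.025 for each of the two contrasts with control.
- Within each contrast, test in a fixed order and stop at the first non-significant result: the single supplemental screening item (*Intent_Screen_SuppScreen*), then anxiety, then breast cancer worry. The first test must name that item, because the registered screening-intention composite has no scoring rule and cannot be tested as it stands.
- Report question 2, informed, confused and all other outcomes with confidence intervals and no confirmatory claim.
- If question 2 is to be confirmatory, use 0.05/3 for each of the three contrasts and restate the power, naming the outcome and effect size it rests on.
- Data collection ended on 30/08/2021. If outcome data had been seen before the rule was written, label it as added post hoc.

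Each sequence has an error rate of at most 0.025, so two together are bounded at 5%, and alpha for the first item is unchanged. No participants are needed. The cost is that anxiety and worry can be claimed only when the earlier tests in the sequence succeed, and two SAP primaries, informed and confused, become non-confirmatory. The registry numbering is not a declared hierarchy, so the order has to be stated as a choice.
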